## Abstract

**Background:**

Treatment options for the management of moderate to severe plaque psoriasis include phototherapy, oral systemic agents, and biologic therapy. Secukinumab, a fully human monoclonal antibody that selectively targets IL-17A, is the first IL-17 antagonist approved for this patient population. Long-term observational data are required for establishing the true population-based benefit-risk ratio of approved treatments. PURE is a multinational registry that will assess the real-world safety and effectiveness of secukinumab and other approved therapies in the management of patients with moderate to severe psoriasis.

**Methods:**

This is a multinational (Canadian and Latin American), prospective, observational study of adult patients with moderate to severe psoriasis that initiate treatment with secukinumab or other approved therapies as per local standard of care. A total of 2500 patients (1250 per cohort) will be recruited in the practices of hospital and community dermatologists. Decision regarding treatment must have been reached prior to and independent of patient enrollment in the study. The study includes a 5-year follow-up with recommended assessments at Baseline, 3 and 6 months post-Baseline, and every 6 months thereafter. The primary objective of the study is safety. Secondary outcome measures relate to effectiveness (Investigator’s Global Assessment -IGA mod 2011-, Psoriasis Areas and Severity Index, Body Surface Area), patient reported outcomes (Dermatology Life Quality Index, Work Productivity and Activity Impairment Questionnaire, Hospital Anxiety and Depression Scale, Psoriasis Epidemiology Screening Tool, Psoriasis Symptom Diary, and Treatment Satisfaction Questionnaire), and healthcare resource utilization.

**Discussion:**

This is the first observational study in Canada and Latin America assessing the real-world safety and effectiveness of secukinumab in the management of moderate to severe psoriasis. The extensive clinical, patient-reported and health economic outcomes collected will allow the comprehensive evaluation of this new treatment in comparison to other approved therapies.

**Trial registration:**

ClinicalTrials.gov Identifier: NCT02786186; date of registration: May 30, 2016.

## Background

Psoriasis is a chronic, immunologically-mediated dermatosis that is estimated to affect 2–3% of the Canadian population [1]. In Latin America, prevalence rates have been estimated to range between 1 and 3% though the actual prevalence is unknown. Chronic plaque psoriasis is the most frequent clinical presentation, and accounts for 90% of all cases. Along with physical discomfort, psoriasis is associated with depression, sexual impairment, social stigmatization and reduced work productivity [1, 2]. Up to 15.5% impairment in work productivity and 23.7% impairment in total activity have been reported to be associated with psoriasis [2]. Consequently, although generally non-fatal, this disease incurs a significant impact on quality of life both physically and psychosocially [1, 3], with reports of reduction in physical and mental functioning comparable to that seen in other chronic diseases [4].

In recent years, the attention paid to psoriasis-related comorbidities has amplified, and a distinct pattern of chronic disorders was found to be significantly associated with psoriasis, including psoriatic arthritis, diabetes mellitus type II, arterial hypertension, hyperlipidemia, and coronary heart disease [5–7]. The combined presence of these conditions, together with obesity, known as the metabolic syndrome, is more prevalent in psoriasis patients than the general population [6, 8]. As awareness of the association of chronic inflammatory diseases and metabolic and vascular diseases increases, it has been suggested that the anti-inflammatory properties of psoriasis treatment modalities may provide therapeutic or preventive benefit related to reduction of cardiovascular- and metabolic-related risk in psoriasis patients.

According to the most recent Canadian Guidelines for the management of plaque psoriasis, moderate to severe psoriasis is distinguished from milder disease in that it is, or would be expected to be, refractory to topical monotherapy [9, 10]. Consequently, the dermatologist’s toolkit for the treatment of moderate to severe plaque psoriasis is broad, and the current Canadian psoriasis guidelines recommend the following therapeutic options: topical calcipotriol–betamethasone dipropionate combination ointment, phototherapy (UVA with psoralen and UVB), oral systemic agents (cyclosporine, methotrexate, and acitretin) and biologic therapy. Similar treatment guidelines have been published for Latin American countries [11–13]. Until 2015, the only biologic therapies approved for the treatment of moderate to severe plaque psoriasis were anti-TNF and IL-12/23 targeting agents. With the introduction of secukinumab, the first IL-17 antagonist approved for moderate to severe plaque psoriasis, the treatment armamentarium was further expanded.

Even though secukinumab was shown to be safe and effective in controlled clinical trials, its long-term safety and effectiveness in the real-world management of moderate to severe plaque psoriasis is yet to be shown. Furthermore, in light of the constantly evolving therapeutic environment, it is important to evaluate how the introduction of secukinumab affects medical decision making in terms of patient selection for treatment with each therapy. The purpose of this observational registry will be to describe the safety, long term effectiveness, and impact on quality of life of secukinumab and other indicated therapies administered to patients with moderate to severe chronic plaque psoriasis in a real-world setting.

## Methods / design

### Objectives

The overall aim of PURE is to provide real-world evidence regarding the safety and effectiveness of secukinumab or other indicated therapies, including locally approved systemic, phototherapy, or biologic therapy alone or in combination.

### Primary objective

To describe the long-term safety profile of secukinumab and other indicated therapies in patients with moderate to severe chronic plaque psoriasis.

### Secondary objectives

To describe the long-term effectiveness, including clinical and quality of life, of secukinumab and other indicated therapies in patients with moderate to severe chronic plaque psoriasis.To describe the long-term impact on productivity of treatment with secukinumab and other indicated therapies in patients with moderate to severe chronic plaque psoriasis.To describe the patient profile, with respect to demographics and clinical features, in patients with moderate to severe chronic plaque psoriasis treated with secukinumab and other indicated therapies.To describe the rate of treatment discontinuation and durability of treatment in patients treated with secukinumab and other indicated therapies for moderate to severe chronic plaque psoriasis.To describe the physical and mental health status of patients treated with secukinumab and other indicated therapies for moderate to severe chronic plaque psoriasis.To describe satisfaction with treatment with secukinumab and other indicated therapies in patients with moderate to severe chronic plaque psoriasis.To describe the socioeconomic impact of disease for patients treated with secukinumab and other indicated therapies in patients with moderate to severe chronic plaque psoriasis.

### Study design

PURE is a multinational, prospective, observational cohort study conducted in the practices of hospital and community dermatologists in Canada and Latin America (Argentina, Brazil, Costa Rica, Guatemala, Mexico, Panama) that treat patients with moderate to severe chronic plaque psoriasis. [14] Patients with moderate to severe chronic plaque psoriasis whom, prior to and independent of study enrollment, the treating physician has decided to treat with an indicated approved regimen as per standard of care in each participating country.

Patients are followed for up to 5 years from the time of enrollment. In accordance with the observational nature of the study, no assessment visits are imposed for the exclusive purpose of the study, however follow-up visits are recommended at 3 and 6 months post-baseline and every 6 months thereafter. Furthermore, any changes in the management of the patient including, but not limited to, changes in medication dose or frequency, termination of a medication or initiation of a new treatment is at the sole discretion of the treating physician and is to be recorded in the study data collection forms. At any time, patients may be withdrawn from the study by the treating physician or on the patient’s expressed choice.

There are two distinct patient cohorts in the study, those that initiate treatment with secukinumab and those that initiate treatment with other indicated and country-approved therapies as per local standard of care. Given the longitudinal nature of the study, it is anticipated that treatment cohort cross-over can occur. All patients will be followed in the study regardless of and after treatment cross-over, as long as they continue to fulfill the study inclusion and exclusion criteria. All analyses will be based on the intent-to-treat (ITT) principle even though treatment cohort may be considered as a time-dependent variable in some analyses.

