#### Inclusion criteria

Able to give written informed consent.At least 18 years of age at time of informed consent signature.Confirmed diagnosis of moderate to severe chronic plaque-type psoriasis diagnosed by a specialist and presence of moderate to severe psoriasis symptoms according to the physician’s clinical judgment at the time of recruitment.Patient is initiating a treatment for psoriasis as per regional policy. This may include secukinumab, other biologics, systemic treatments, and phototherapy. Decision to treat with any of the above-mentioned treatments must have been reached prior to and independently of recruitment in the study.Treatments are prescribed in accordance to the product monograph and regional regulatory and reimbursement policies.Patient is able to understand and communicate with the investigator and comply with the requirements of the study.

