#### Outcome variables

The primary outcome variable will be the incidence of total AEs, total serious AEs (SAEs) and infections, as measured by the proportion of patients with at least one event, the mean number of events per patient, and the mean number of events per person-year of follow up. All adverse events will be mapped, based on the following hierarchy of exposures (in descending order of priority): [1] secukinumab, [2] other, [3] and non-biologic agents.

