### Statistical methods

#### Sample size considerations

This is an observational study aimed at describing the safety, effectiveness and patient reported outcomes in patients treated with secukinumab and other indicated approved therapies for moderate to severe chronic plaque psoriasis. Given the observational nature of the study, sample size considerations are based on the precision of measuring the primary outcome measure, namely the incidence of total adverse events (AEs), total serious AEs (SAEs) and infections, as measured with the width of the 95% confidence interval (CI).

With 1250 patients in the secukinumab cohort, and assuming an incidence rate of 60% for total AEs, the 95% CI will be 60% ± 3%, or 5% of the point estimate; for SAEs, assuming an incidence of 5%, a sample size of 1250 patients will yield a 95% CI of ±1.2% or 24% of the point estimate; for infections, assuming an incidence of 30%, a sample size of 1250 patients will produce a 95% CI of ±3%, or 10% of the point estimate. All within acceptable level of precision.

Although the primary aim of the study will be to describe the incidence of AEs in the two study cohorts, between cohort comparisons may be conducted for descriptive/exploratory purposes only without any a-priori hypothesis testing. With 1250 patients per cohort, the study will be able to detect with 90% power and 5% significance, an odds ratio of 1.30 for any adverse event, an odds ratio of 1.75 for SAEs, and an odds ratio of 1.35 for infections.

Approximately 80% are planned to be recruited from Canada and 20% from the participating Latin American countries.

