### Statistical analyses

AEs and SAEs will be summarized for the two treatment cohorts using the total number of events, the total number of patients and percentage of patients who experienced at least one event within each body system and within each preferred term of the Medical Dictionary for Regulatory Activities (MedDRA); in these descriptive analyses, crossed-over patients (to either direction) will be described as a separate treatment cohort. Within each treatment cohort, patients experiencing the same event multiple times will be only counted once for the corresponding preferred term and body system. Relative risk/odds and incidence density rate ratio will be estimated to assess the difference between cohorts.

The levels of all physician-reported and patient-reported outcomes will be described for all visits by baseline treatment cohort; between-cohort differences will be assessed using the independent-samples t-test (or non-parametric alternative, as needed) for continuous variables and the chi-square test for categorical variables. In addition, the absolute changes in IGA, PASI, and BSA, will be described and the paired t-test will be conducted to assess the within-group change from baseline at each visit. Multivariate mixed models with repeated measures that may adjust for potential confounders will be used to assess the levels of each of these continuous parameters (IGA, PASI, BSA, DLQI, HADS, PEST, WPAI and PSD) over the five-year follow up period of the study.

For each visit, achievement of therapeutic endpoints, specifically IGA ≤ 1, IGA = 0, PASI 50, 75, 90 and 100 and DLQI ≤1 will be described with the proportion within each treatment cohort. Between-cohort differences will be assessed with generalized estimating equations. Time to achieving therapeutic endpoints, specifically IGA ≤ 1, IGA = 0, PASI 50, 75, 90 and 100 and DLQI ≤1, and the durability of response will be described with the Kaplan-Meier estimator. Between-cohort differences will be described with the log-rank test. Furthermore, Cox’s proportional hazards models that may adjust for potential confounders will be used to compare the two treatment cohorts.

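### Between-cohort comparisons use a comparator that pools other biologics, oral systemics and phototherapy in no set mix; results by comparator class should be added

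*Protocol article*

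**What the plan says.** The Study design section of the protocol article fixes the cohorts: "There are two distinct patient cohorts in the study, those that initiate treatment with secukinumab and those that initiate treatment with other indicated and country-approved" (…). The Inclusion criteria list what a patient may be starting: "This may include secukinumab, other biologics, systemic treatments, and phototherapy". The Objectives add that these therapies count "including locally approved systemic, phototherapy, or biologic therapy alone or in combination". Everything that is not secukinumab therefore falls into one comparator.

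On numbers, the abstract says: "A total of 2500 patients (1250 per cohort) will be recruited in the practices of hospital and community dermatologists". The only planned split is by region: "Approximately 80% are planned to be recruited from Canada and 20% from the participating Latin American countries". No share or quota by therapy class is given, and treatments follow regional regulatory and reimbursement policy.

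The Statistical analyses section works with these cohorts throughout: relative risk or odds and rate ratios for adverse events; t-tests and chi-square tests by baseline cohort; generalized estimating equations for responder endpoints; log-rank tests; and "Cox’s proportional hazards models that may adjust for potential confounders will be used to compare the two treatment cohorts". Crossed-over patients form a separate group, but only in the descriptive adverse-event summaries.

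The Outcome variables section uses a different division. Adverse events are mapped by a "hierarchy of exposures (in descending order of priority): [1] secukinumab, [2] other, [3] and non-biologic agents". Level 2 presumably means other biologics, since non-biologics have their own level, but the text does not say so.

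**The concern.** A pooled comparator's event rate is a weighted average of its classes, and here the weights are set by local prescribing and reimbursement. If outcomes differ between biologics and non-biologics, the secukinumab-versus-pool ratio moves with those weights even when nothing about secukinumab changes. The ratio can lie above or below 1 although secukinumab and the other biologics are identical.

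Adjusting for confounders does not remove this. Adjustment makes the patients more alike; it does not change the therapies that make up the comparator. The one covariate that would help is therapy class itself, and a model containing it is the class comparison that the article does not state.

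This matters because the abstract promises an evaluation in comparison with other approved therapies, and the Discussion names policy makers among its readers. Such readers may take a pooled ratio as evidence about secukinumab against its nearest alternatives.

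**Working it through.** **The plan's own figures.** Inputs from Sample size considerations: 1250 patients per cohort; 60% any adverse event, 5% serious, 30% infections; detectable odds ratios of 1.30, 1.75 and 1.35 with 90% power at 5% significance.

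- Half-width = 1.96 × √(p(1−p)/1250). This gives 2.7 points at 60%, 1.2 at 5% and 2.5 at 30%, against the stated 3, 1.2 and 3. They agree after rounding.
- Two-sided power of a two-proportion test at the stated odds ratios: 88.6% to 90.1% for any adverse event and 91.4% to 94.2% for infections, depending on direction; 93.0% for serious events when the odds ratio is read upward from 5% (76% if read downward).

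These figures are not in dispute. They hold for 1250 against 1250, which means the pooled comparison.

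**Dependence on mix.** Let w be the share of non-biologics in the comparator. Let p_b be the rate on any biologic, with secukinumab set equal to it, and p_n the rate on non-biologics.

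- Comparator rate: p_c = (1−w) × p_b + w × p_n
- Pooled odds ratio: [p_b/(1−p_b)] / [p_c/(1−p_c)]

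Infections, with p_b = 30% (the plan's figure for the secukinumab cohort) and p_n = 20% (assumed):

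- w = 20%: p_c = 0.8 × 0.30 + 0.2 × 0.20 = 0.28; OR = 0.4286/0.3889 = 1.10
- w = 50%: p_c = 0.25; OR = 0.4286/0.3333 = 1.29
- w = 60%: p_c = 0.24; OR = 0.4286/0.3158 = 1.36, about the 1.35 that the plan says it can detect
- w = 80%: p_c = 0.22; OR = 0.4286/0.2821 = 1.52

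The table repeats this for other assumed rates. Each cell gives the pooled odds ratio and, in brackets, the chance of two-sided p < 0.05 with 1250 per cohort.

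| Outcome (any biologic / non-biologic) | w = 20% | w = 50% | w = 80% |
|---|---|---|---|
| Infections, 30% / 20% | 1.10 (20%) | 1.29 (80%) | 1.52 (>99%) |
| Infections, 30% / 25% | 1.05 (8%) | 1.13 (28%) | 1.22 (61%) |
| Any adverse event, 60% / 50% | 1.09 (17%) | 1.23 (72%) | 1.38 (98%) |
| Serious adverse event, 5% / 3% | 1.09 (7%) | 1.26 (23%) | 1.50 (51%) |
| Responder endpoint, 60% / 30% | 1.28 (86%) | 1.83 (>99%) | 2.67 (>99%) |

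In every cell the true odds ratio of secukinumab against other biologics is 1.00. All non-biologic rates, both responder rates and every value of w are assumptions. The document supplies only the 30%, 60% and 5%, as planning rates for the secukinumab cohort.

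**The two sections side by side.** Outcome variables treats non-biologic agents as an exposure of their own. Statistical analyses reports adverse events and ratios by the two cohorts, plus crossed-over patients, and no stated effectiveness comparison uses the finer division.

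**The case against.** The study does not rest on these comparisons. The primary and all secondary objectives are to describe, and the sample size is justified by the precision of the secukinumab estimates, which the comparator mix cannot touch. Sample size considerations also calls the between-cohort comparisons exploratory and without prior hypotheses. All of this stands and limits the weight of the point. It does not make a mix-dependent ratio easier to interpret once reported.

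An analysis plan not shown may contain class-level analyses, and the adverse-event hierarchy suggests that class-level safety reporting was considered. That is fair. The point is therefore confined to what the article fixes: a two-cohort contrast for its comparisons, and an exposure hierarchy that does not match it.

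The sizes are illustrative. With a 5-point infection gap and 20% non-biologics the odds ratio is only 1.05. The mechanism is certain whenever the classes differ; its size here is unknown.

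Splitting into two classes still leaves some pooling: anti-TNF with IL-12/23 agents, and oral systemics with phototherapy. This is also true. The split reduces dependence on mix but does not abolish it.

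Three stronger readings are tempting and are not supported:

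- A reader might infer that the pooled contrast answers no treatment question. Secukinumab initiators against initiators of other local standard care is a recognisable registry contrast, and an unset mix follows naturally from treatment being chosen independently of enrolment.
- A reader might infer that completed phototherapy courses distort the time to treatment discontinuation. The article does not say how phototherapy is given or that completion counts as discontinuation. It collects reasons for discontinuation, and its log-rank and Cox comparisons are described for therapeutic endpoints and durability of response.
- A reader might infer that secukinumab versus other biologics must lead. Nothing in an exploratory plan requires such a ranking.

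**Conclusion.** The point holds as a limit on the between-cohort comparisons and as a mismatch between two sections. The pooled odds, rate and hazard ratios depend on an unspecified comparator mix and can differ from 1 with no difference between secukinumab and other biologics. Under the assumed infection rates of 30% on biologics and 20% or 25% on non-biologics, the pooled odds ratio runs from 1.05 to 1.52 as the non-biologic share goes from 20% to 80%. The direction and size in the real registry cannot be known from the document, because it gives neither the mix nor rates by class. The primary descriptive results for secukinumab are not affected, and the plan is not invalid. The change is a worthwhile improvement because it needs no new data.

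**What to change.** Leave enrolment as it is, and keep the pooled contrast, labelled as secukinumab versus local usual care. Then:

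1. In Statistical analyses, also report the safety and effectiveness summaries and comparisons by class of index treatment: secukinumab versus other biologics, and secukinumab versus non-biologic therapy (systemics and phototherapy). Class a comparator combination that includes a biologic as biologic.
2. In Outcome variables, name level 2 of the exposure hierarchy and align the levels with these classes.
3. In Sample size considerations, state that the detectable odds ratios apply only to the pooled comparison.
4. Report the achieved comparator mix beside every pooled ratio.

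The cost is analysis wording and extra tables. The treatment being initiated already determines cohort entry, and current psoriasis therapies are recorded at baseline. The real downside is precision, because each class has fewer than 1250 comparators. For a 30% infection rate the half-width of 1.96 × √(0.21/n) is 2.5 points at n = 1250, 3.6 at n = 625 (a class holding half the cohort) and 5.7 at n = 250 (a fifth). Class comparisons will detect only larger odds ratios than those now quoted.

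### Follow-up is made conditional on patients still meeting the entry criteria, which puts the 5-year safety and durability estimates at risk of informative censoring

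*Protocol article*

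**What the plan says.** All references are to the protocol article. Under Study design, "Patients are followed for up to 5 years from the time of enrollment". The same section then says "All patients will be followed in the study regardless of and after treatment cross-over", and the sentence ends with a condition: "as long as they continue to fulfill the study inclusion and exclusion criteria". The next sentence states "All analyses will be based on the intent-to-treat (ITT) principle", while allowing cohort to be time-dependent in some analyses. Earlier in the section, changes of dose or frequency, stopping a drug and starting another are left to the physician: any such change "is at the sole discretion of the treating physician and is to be recorded in the study data collection forms".

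The Inclusion criteria contain two items with no time anchor that could cease to hold: "Treatments are prescribed in accordance to the product monograph and regional regulatory and reimbursement policies" and "Patient is able to understand and communicate with the investigator and comply with the requirements of the study". The Exclusion criteria add two that could newly apply: being unwilling or unable to comply, and taking part in another interventional or non-interventional trial, either concurrently or in the preceding 30 days.

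The primary outcome (Outcome variables) is total AEs, SAEs and infections. Each is expressed as the proportion of patients with an event, the mean number of events per patient, and events per person-year.

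**The concern.** Entry criteria normally decide who comes in. Here they also decide who stays, and the article neither limits which criteria continue to apply nor says that data are still collected once one lapses.

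The events that could make a criterion lapse are not neutral. Use outside the monograph, loss of ability to comply and entry into another trial may each follow poor response, intolerance or illness. If observation stops at those points, the remaining person-time is selected on something related to outcome. Long-term safety is the primary objective, and the Kaplan-Meier and Cox analyses under Statistical analyses rely on censoring being unrelated to later risk. An analysis plan cannot recover data that were never collected, so the matter has to be settled in the protocol.

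**Working it through.** **Step 1: which criteria can lapse.**

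| Criterion | Time anchor in the text | Can it end follow-up? |
|---|---|---|
| Age | at consent | No |
| Moderate to severe symptoms | at recruitment | No, so skin clearance is not an exit route |
| Starting a psoriasis treatment | none | Cannot continue to be met by anyone |
| Prescribing per monograph and regional policy | none | Yes |
| Able to understand, communicate and comply | none | Yes |
| Unwilling or unable to comply (exclusion) | none | Yes |
| In another trial (exclusion) | concurrent or last 30 days | Yes |

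The third row shows that the clause cannot be applied to every criterion. Sites must therefore decide for themselves which ones continue, across seven countries (Canada and six in Latin America) whose labels and reimbursement rules may differ.

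**Step 2: the clause beside its neighbours.** A treatment change made at the physician's discretion and duly recorded could, if it departs from the monograph or regional policy, end the patient's eligibility for follow-up. An analysis by baseline cohort under ITT needs outcomes after such changes. The Discussion counts the observation of cross-overs and treatment changes as a strength of the registry. The clause works against all three.

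**Step 3: the plan's own precision, for scale.** Half-width = 1.96 × √(p(1−p)/n), with n = 1250 per cohort (Sample size considerations):
- AEs, p = 0.60: ±2.72 points (stated ±3%).
- SAEs, p = 0.05: ±1.21 points (stated ±1.2%).
- Infections, p = 0.30: ±2.54 points (stated ±3%).

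These agree after rounding. If 20% of patients contributed nothing (n = 1000), the half-widths would be 3.04, 1.35 and 2.84 points. Precision is therefore not the problem; selection is.

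**Step 4: illustrative bias in the person-year rate.** The exit fraction d, exit at 2.5 of 5 years and the post-exit rate multiple k are all assumptions; the article gives none of them. Let the base rate be λ, and let leavers have rate λ before exit and kλ after.
- Observed rate = λ.
- True rate = λ[(1−d)·5 + d(2.5 + 2.5k)]/5 = λ[1 + d(k−1)/2].
- Understatement = 1 − 1/[1 + d(k−1)/2].

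| k | d = 5% | d = 10% | d = 20% |
|---|---|---|---|
| 1 | 0% | 0% | 0% |
| 1.5 | 1.2% | 2.4% | 4.8% |
| 2 | 2.4% | 4.8% | 9.1% |
| 3 | 4.8% | 9.1% | 16.7% |

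If k is below 1, the sign reverses and the observed rate is too high.

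**Step 5: a different pre-exit assumption.** If leavers have three times the base rate throughout, observed/true = [(5+2.5d)/(5−2.5d)]/(1+2d). At d = 10% this is (5.25/4.75)/1.2 = 0.921, or 7.9% low. At d = 20% it is (5.5/4.5)/1.4 = 0.873, or 12.7% low.

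**Step 6: the measures without person-time.** Mean events per patient is not corrected for shorter follow-up. Even with k = 1, the observed five-year mean is 1 − d/2 of the full one: 2.5% low at d = 5% and 10% low at d = 20%. The proportion with at least one event also falls with early exit.

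**The case against.** The strongest reply is that the clause is loose wording rather than an operating rule. Read literally it would empty the study soon after baseline, since nobody keeps starting treatment. The Patient population section presents the criteria as conditions of inclusion, and the article describes no eligibility re-check and no removal procedure. This stands as far as it goes: a reader might infer that such patients are in fact dropped and the data are informatively censored, and the document does not show that. It does state the condition, though, and nothing in it restricts the condition.

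Other points also stand in part:
- Physician or patient withdrawal is separately allowed at any time and no visits are imposed, so some patients who cannot comply would leave with or without the clause.
- Departure from the monograph could follow good response or a reimbursement change as well as failure, so the direction of bias is not fixed.
- Events up to exit are counted, including a loss of response or discontinuation that came first.
- Likelihood-based mixed models remain valid if exit depends only on outcomes already recorded.
- A qualifier within a sentence limits it rather than flatly contradicting it; cross-over alone is still not a reason to stop.
- Ending follow-up at entry to another trial can be defended in a registry of approved therapies. Recording the date and censoring in a sensitivity analysis achieves the same without losing the data.

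These points reduce the likely size of the effect. None of them limits the clause or restores data after a criterion lapses.

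**Conclusion.** The point holds as a risk created by a stated rule. Follow-up depends on criteria that can lapse for outcome-related reasons, and one criterion makes the rule impossible to apply in full. The primary incidences, person-year rates and durability estimates are at risk of informative censoring, and the clause sits badly with the ITT sentence and the real-world aim.

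The stronger conclusion, that long-term harm is understated and durability overstated by a known amount, is not supported: the article gives no exit rate, exit time or post-exit event rate. On the assumptions in Step 4, the bias in the person-year rate runs from none (later rate unchanged), through 1-5% low (1.5 times), to 5-17% low (three times, the extreme of the grid). Nor can it be said how far between-cohort ratios would be distorted. That depends on exit differing by cohort, and those comparisons are described as exploratory. The change is worth making because it is nearly free and removes an avoidable exit route from the primary data.

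**What to change.** Delete the condition in Study design and state that inclusion and exclusion criteria are judged at enrollment only. Enrolled patients are then followed for up to 5 years, until death, or until withdrawal by the patient or physician as the section already allows, whatever their later prescribing status. The right of physician withdrawal is left untouched. Record off-monograph use and entry into another study with dates, so that sensitivity analyses can censor at those points and be set beside the main ITT analysis.

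The cost is a short amendment, the date fields, and a few more follow-up records on patients already enrolled. If the sponsor never intended to stop follow-up in these cases, the amendment only brings the text into line with practice.
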